## Abstract

**Background:**

Intertrochanteric fracture (ITF) is increasing with the rapid increase in the aging population, often causes a high mortality rate in old patients and increases the economic burden of the family and society. ERAS (Enhanced Recovery after Surgery) is a powerful guarantee for patients to accelerate their recovery after surgery. TCM (traditional Chinese medicine) promotes repair of injured tissues and eliminates traumatic aseptic inflammation. Therefore, this prospective randomized controlled clinical trial aims to evaluate the clinical effect of the evidence-based ERAS pathway of integrating TCM with western medicine on perioperative outcomes in ITF patients undergoing intramedullary fixation and provide reliable evidence-based data for applying the program to clinical practice.

**Methods/design:**

We will conduct a prospective randomized, blinded, controlled trial to compare the effectiveness of ERAS care pathway with traditional care pathway and to investigate whether the ERAS care pathway can improve the perioperative outcome in ITF patients undergoing intramedullary fixation. A total of 60 patients with ITF will be enrolled and treated with the two care pathway, respectively. Length of stay, economic indicators, Harris score, VAS score, time to get out of bed, 30-day readmission rates, postoperative transfusion rates, discharge to home, and mortality will be evaluated. Any signs of acute adverse reactions will be recorded at each visit during treatment.

**Discussion:**

Although an evidence-based process using the best available literature and Delphi expert-opinion method has been used to establish an ERAS pathway of integrating TCM with western medicine, there is a lack of consensus about its effectiveness. This trial will provide convincing evidence about the effect of ERAS pathway.

**Trial registration:**

Registered on 12 October 2019. Trial number is ChiCTR1900026487.

## Introduction

With the aging of society, the incidence of intertrochanteric fracture (ITF) is increasing. It is easy to bring bedsore, urinary tract infection, lung infection, and other complications. Intertrochanteric fracture has become a major public health issue with a high mortality rate for old patients and increased the economic burden [1, 2]. Currently, ITF is treated with both surgical and non-surgical methods. Surgical treatment has great advantages in alleviating pain, restoring hip function, improving quality of life, and avoiding complications such as deep vein thrombosis and cardiovascular accident caused by long-term bed rest, so surgical treatment is the first choice of treatment [3–6]. Currently, PFNA (proximal femoral nail anti-rotation, PFNA) is a mature surgical treatment for senile ITF, which is characterized by maintaining strong fixation, biomechanical stability, and minimal invasion [7, 8].

ERAS (Enhanced Recovery after Surgery) is one of the two important development directions leading the development of modern surgery in the twenty-first century, which is first proposed by Kehlet in 1997 [9]. ERAS aims to integrate the perioperative diagnosis and treatment concept by optimizing a series of effective approaches and methods with evidence-based medical evidence, so as to reduce trauma invasion and alleviate the stress reaction caused by surgery. The core of the ERAS is a powerful guarantee for patients to accelerate their recovery after surgery [10–13]. At present, ERAS has been applied in the treatment of many orthopedic diseases including artificial joint replacement [14].

Currently, major efforts are being conducted to transfer the lessons learned from other surgical specialties and incorporate ERAS protocols into postoperative care of patients undergoing hip surgery. ERAS protocols for artificial joint replacement have been described that it can reduce postoperative mortality and increase satisfaction for patients. However, to our best knowledge, ERAS programs for patients with ITF have not been described. Furthermore, traditional Chinese medicine including acupuncture, manipulative therapy, and oral Chinese medicine can improve blood circulation in local tissues, relax tense and spasmodic muscles, promote repair of injured tissues, and eliminate traumatic aseptic inflammation. Therefore, it is of great significance to establish an effective plan and management pathway integrated Chinese and western medicine to accelerate postoperative recovery of ITF. With the objective in mind, we have conducted a systematic literature search to guarantee the comprehensiveness of the study; Delphi expert-opinion method was used to establish the ERAS pathway. Here, ERAS programs consist of a multidisciplinary evidence-based approach to preoperative management, intraoperative control, and rehabilitation for ITF, and preoperative multidisciplinary collaboration had been already established.

Therefore, this prospective, randomized, controlled clinical trial aims to evaluate the clinical effect of an evidence-based ERAS pathway integrated Chinese and western medicine on perioperative outcomes in ITF patients undergoing intramedullary fixation and provide reliable evidence-based data.

## Materials and methods

### Study design

This study is a prospective, outcome assessor- and data analyst-blinded, randomized controlled design study that compared an ERAS care pathway cohort with standardized care pathway cohort. Emergency admissions with a primary diagnosis of ITF between January 2020 and July 2021 in our hospital will be selectively enrolled. All patients will receive their operation at our hospital where elective surgeries take place predominantly, and they will be treated with PFNA intramedullary fixation at our institution.

The objective of this proposed study is to investigate whether ERAS care pathway will lead to perioperative improvement in ITF patients undergoing intramedullary fixation. The principal investigator (PI) is responsible for the overall project and organizing Steering Committee meetings. PIs of sub-center departments are responsible for gathering experts to carry out the project. An independent Steering Committee will be responsible for affairs such as participants’ safety, meetings, recruitment and follow-up of participants, and quality control. The coordinating center is responsible for communicating protocol modifications and providing materials. This trial includes a 2-week treatment period and a 3-month follow-up period. Outcome assessments will be conducted at baseline, as well as at 3, 14, 30, and 90 days (Fig. 1).

**Fig. 1 Fig1:**
[figure not shown]
Participant processing and the schedule of evaluation

### Eligibility criteria

#### Inclusion criteria

Participants who meet the criteria below are eligible [15]:
The patients are over 75 years old.X-ray or CT indicates unstable ITF.Treated with PFNA intramedullary fixation.Being willing to undergo surgery with the ERAS pathway.Being willing to give informed consent.

#### Exclusion criteria

The exclusion criteria are as follows [15]:
Patients are with open fractures or pathological fracture caused by tumor, infection, or tuberculosis.Patients are with congenital hip dysplasia or osteonecrosis of the femoral head.Hip surgery before enrollment.Failure to understand or sign informed consent.

### Patient population and recruitment procedure

Participants will be recruited from Longhua Hospital affiliated to Shanghai University of Traditional Chinese Medicine. Prospective participants will be interviewed by the coordinators and informed of the eligibility criteria and the procedure. Those who are eligible and willing to participate in the study will be screened initially by baseline assessment and then diagnosed based upon clinical manifestations, physical examination, and imaging. Participants will be informed that participating in the trial was absolutely voluntary and withdrawal from the trial can be made at any time. In case of withdrawal, the data collected will not be deleted and will be used in the final analyses. A data compilation form including all variables of interest and all potential risks will be completed by the corresponding research center. The information obtained will be stored in an electronic database for subsequent statistical analysis. Recruitment will start in January 2020 and is expected to end in July 2021. The final follow-up of all participants will be completed on 30 September 2021. The overview of the participant processing and the schedule of evaluation is provided in Fig. 1.

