### Safety assessments

Infection, deep venous thrombosis, and cardiovascular accidents will be recorded at each visit during treatment.

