To our best knowledge, our study is the first elaborately designed, randomized, controlled trial to evaluate the clinical effect of the ERAS project integrated Chinese and western medicine on perioperative outcomes in ITF patients undergoing PFNA. A hallmark of ERAS is coordination between care services before and after surgery and continual evaluation of postoperative course with attention toward pain control, functional recovery, and patient satisfaction to improve standards of care. So the study is designed as a comprehensive study of LOS, economic indicators, pain relief, functional outcome, and complications. Outcome measurements are widely used in research to establish baselines, evaluate the effect of an intervention, and motivate patients’ self-evaluation. LOS was the most commonly assessed metric in comparative analyses. And a comparative reduction in LOS was reported in most studies using the ERAS protocol. Improved cost-effectiveness of surgical interventions is also a primary objective when implementing strategies for faster recovery in this study. The calculation of cost-effectiveness provided is based on data provided by our Department of Finance. The study is also to evaluate whether ERAS program can lead to a reduction in hospitalization costs, care costs, and nursing costs, which supports the cost-effectiveness of “fast-track” protocols in PFNA surgery. The VAS measurements, which have been found valid, reliable, and easy to apply in researches, are often used as the criterion standard to evaluate the pain intensity. The Harris score, a self-administered questionnaire, has been widely adopted as the criterion standard to estimate disease activity for its reliability and validity. Another aim of the study lies in reducing both intra- and postoperative adverse events and complication, which have the potential to impair the patients’ perioperative well-being and to prolong recovery. Especially in elderly patients, or in those with severe comorbidities, strict patient selection is key to both eligibility for safe ERAS and treatment in specialized short-stay clinics that may not have an ICU available. Administration of prophylactic medication against infections and thrombosis, prevention of hypothermia, and fluid imbalance, as well as operative measures, has therefore become integral to successful implementation of ERAS [27–30].

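### Follow-up closes on 30 September 2021, too early for the day-90 visit of anyone enrolled after 2 July 2021, and the named safety events have no stated recording after the 2-week treatment

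*Protocol article*

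**What the plan says.** Four statements in the protocol article bear on the calendar.

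- Recruitment (Patient population and recruitment procedure): "Recruitment will start in January 2020 and is expected to end in July 2021". Study design gives the same window: "Emergency admissions with a primary diagnosis of ITF between January 2020 and July 2021 in our hospital will be selectively enrolled". Neither gives a day of the month.
- Close of follow-up (Patient population and recruitment procedure): "The final follow-up of all participants will be completed on 30 September 2021".
- Length of participation (Study design): "This trial includes a 2-week treatment period and a 3-month follow-up period".
- Visits (Study design): "Outcome assessments will be conducted at baseline, as well as at 3, 14, 30, and 90 days".

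Two statements set the window for recording harms. Safety assessments says: "Infection, deep venous thrombosis, and cardiovascular accidents will be recorded at each visit during treatment". The abstract has a parallel sentence: "Any signs of acute adverse reactions will be recorded at each visit during treatment". The Discussion names "reducing both intra- and postoperative adverse events and complication" as a further aim of the study.

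Statistical analyses applies last observation carried forward to missing data on all measures.

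**The concern.** The enrolment window, the visit schedule and the closing date are all fixed in the article, and for most of July 2021 they cannot all be met. A late-enrolled patient would lose the day-90 visit because of the plan itself, not because of dropout. The carry-forward rule would then put an earlier value, normally that of day 30, in place of the day-90 Harris and VAS scores. Function and pain may well still be changing between those two visits.

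The safety wording raises a different problem with the same visits. Patients are to be seen at days 30 and 90, but the sentence that governs the three named complications stops at the end of treatment. Infection, thrombosis and cardiovascular events arising after day 14 would then have no stated place of recording, in a trial that aims to reduce postoperative complications.

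**Working it through.** **Inputs.** Recruitment runs from January 2020 to July 2021 (Study design; Patient population and recruitment procedure). Follow-up closes on 30 September 2021 (Patient population and recruitment procedure). The last assessment is at day 90, with 2 weeks of treatment and 3 months of follow-up (Study design). The planned total is 72 (Sample size calculation); the abstract gives 60.

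**Step 1: can the closing date be reproduced?** Last enrolment that fits = closing date − 90 days = 30 September 2021 − 90 days = 2 July 2021. The stated date is therefore consistent with the schedule only if recruitment stops on 1 or 2 July and day 90 counts from baseline.

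| Enrolled | Days available to 30 September | Day 90 falls on | Shortfall |
|---|---|---|---|
| 1 July 2021 | 91 | 29 September | none |
| 2 July 2021 | 90 | 30 September | none |
| 15 July 2021 | 77 | 13 October | 13 days |
| 31 July 2021 | 61 | 29 October | 29 days |

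**Step 2: how many patients?** The article gives no accrual curve and no closing day in July. Assume even accrual from 1 January 2020.

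- Recruitment to 31 July 2021: the window is 366 + 212 = 578 days. Late days are 3 to 31 July, which is 29. 29/578 = 5.0%, or 0.050 × 72 = 3.6 patients (3.0 of 60).
- Recruitment to 15 July 2021: the window is 366 + 196 = 562 days, with 13 late days. 13/562 = 2.3%, or 1.7 of 72 patients.
- Recruitment to 2 July 2021 or earlier: none.

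**Step 3: the other reading of 3 months.** If follow-up starts after the 2-week treatment, participation lasts 14 + 90 = 104 days. The last enrolment that fits is then 18 June 2021, and a patient enrolled on 31 July finishes on 12 November. Late days would be 43, and 43/578 = 7.4%, or 5.4 of 72. The article lists no visit after day 90, so this reading shows that the starting point is unclear; it does not identify a visit that would be missed.

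**Step 4: which outcomes are exposed?** Length of stay and costs are settled by discharge. For 30-day readmission, 31 July + 30 days = 30 August. If the 30 days count from discharge, a patient enrolled on 31 July still fits with any stay of up to 61 − 30 = 31 days; the pilot values were 5.8 and 9.2 days. Day-90 Harris and VAS are exposed, assuming both are measured at every listed visit. Mortality has no stated time point, so whether it is exposed cannot be settled from the text.

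**Step 5: the safety window.** Treatment lasts 14 days and the visits after baseline are days 3, 14, 30 and 90. Read literally, recording during treatment covers days 3 and 14, which is 2 of 4 visits and 14/90 = 16% of the follow-up days. That is a share of time, not of events. No sentence in the article assigns the three named events to day 30 or day 90.

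**The case against.** **On the dates.** Recruitment is only expected to end in July, with no day given, and a stop on 1 or 2 July would remove the conflict. The 5% figure takes the latest possible end and even accrual. The primary outcomes are hardly touched. All of this stands and limits the size. It does not reconcile the dates, because the closing date is stated firmly and for every participant.

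**On harms.** A reader might infer that no harm is captured after day 14. The article does not support that. Mortality and 30-day readmission are secondary outcomes and would pick up some serious later events. The data compilation form under Patient population and recruitment procedure is said to cover all potential risks, without a time limit. The schedule of evaluation is in Fig. 1, which could not be read for this review and may list safety items at later visits. What remains is narrower: the sentence on the three named events, as worded, stops at the end of treatment.

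**On bias.** A reader might also infer that a pathway with earlier discharge would look safer than it is. The visit days are the same in both arms, and on the pilot figures of 5.8 and 9.2 days a typical patient in either arm is home before day 14. A short window loses late events in both arms, and nothing in the article shows that the loss would differ between them.

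**Conclusion.** The calendar conflict holds: enrolment after 2 July 2021 is incompatible with a day-90 visit by 30 September 2021. Its effect is small, from none to about 4 of 72 patients (5%) depending on when in July recruitment ends. The upper figure assumes even accrual to 31 July and day 90 counted from baseline. The loss falls on day-90 Harris and VAS, which would be filled by carry-forward; length of stay, in-hospital costs and 30-day readmission are essentially unaffected.

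The safety point holds as a fault of wording, and with less certainty because Fig. 1 was not visible. Infection, deep venous thrombosis and cardiovascular accidents have no stated recording at the two later visits, which fits poorly with the aim of reducing postoperative complications. It is not shown that late harm goes wholly unseen or that either arm is favoured.

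Both points should be corrected, mainly because correction costs so little.

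**What to change.** 1. Set the final follow-up date at least 90 days after the last enrolment, which is 29 October 2021 if enrolment runs to 31 July. Alternatively, close recruitment by 2 July 2021 and keep 30 September.
2. State whether the 3-month follow-up runs from baseline or from the end of the 2-week treatment. If from the end of treatment, recompute the closing date on that basis.
3. Reword the sentence under Safety assessments so that infection, deep venous thrombosis and cardiovascular accidents are recorded at every scheduled visit through day 90. Bring the abstract and Fig. 1 into line.

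The cost is a follow-up close about 4 weeks later (29 days in the latest case) and one safety form at two visits that already exist. No visits are added. Closing recruitment by 2 July instead gives up as much as 4 weeks of enrolment.

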### Patient and public involvement

Patients and/or the public will not be involved in the study design and study enrolment.

### Ethics

This study is to be conducted in accordance with the principles of the Declaration of Helsinki and has been approved by Sichuan Regional Ethics Review Committee on Traditional Chinese Medicine (TCM) [16]. The trials have been approved by the appropriate Institutional Review Boards. The clinical trial has been approved by the Institutional Review Board of Longhua Hospital, Shanghai University of TCM. All participants will be given sufficient time to reach a decision to sign the consent form prior to the study in compliance with Good Clinical Practice Guidelines that guides the appropriate use of TCM in clinical practice. Then, the participants will be randomized into two groups of different treatments. Reporting will be guided by the CONSORT statement [17, 18].

### Intervention

#### ERAS care pathway

An evidence-based process using the best available literature and Delphi expert-opinion method was used to establish the ERAS pathway integrated Chinese and western medicine. The basic components of the multi-disciplinary ERAS pathway which we used are shown in Table 1. The principles include educational program, management of nutrition, management of dietary, management of sleep, management of pain selection of anesthesia, control of bleeding, management of body temperature, prevention of infection, management of anesthesia, management of rehydration management of drainage tube, control of nausea and vomiting, and management of activity.

**Table 1 Tab1:** The basic components of the multi-disciplinary ERAS pathway

Preoperative	Educational program	(1) Understand the patient, assess the condition
		(2) Psychological, nutrition, surgery, rehabilitation education
		(3) Good communication
		(4) Emphasize active function exercise
		(5) Advocate deep breathing, upper limbs pull rings, and other cardiopulmonary exercise
	Management of nutrition	(1) If there is hypoalbuminemia and severe anemia, actively look for the original disease and correct it
		(2) When necessary, human serum albumin 10 g Ivgtt
		(3) Megaloblyte anemia: folate 5–10 mg Po Tid+ vitamin B12 0.5 mg Im Tiw
		(4) Iron deficiency anemia: EPO 10,000 IU Ih Tiw+ ferrous succinate 0.2 g Po Tid
	Management of dietary	(1) Eat a high protein diet
		(2) Before anesthesia 6 h fast protein liquid (such as milk, broth)
		(3) Before anesthesia 4 h fast carbohydrates (such as rice porridge, steamed bread)
		(4) 2 h before anesthesia, do not drink clear liquid
		(5) When necessary, 250–500 ml glucose was dropped 2–3 h before operation
	Management of sleep	(1) Sedative hypnotic or anti-anxiety drugs
	Management of pain	(1) Routine use of anti-inflammatory analgesics such as celecoxib 200 mg Po Bid
Intraoperative	Selection of anesthesia	(1) General anesthesia (laryngeal mask or endotracheal intubation)
		(2) Combined with local infiltration anesthesia: ropivacaine 200 mg + 80 ml saline was injected into the incision and surrounding deep needle
	Control of bleeding	(1) Blood pressure control: systolic blood pressure control in 90–110mmhg
		(2) Bleeding control: 5–10 min before skin incision, tranexamic acid should be dropped 15–20 mg/kg
	Management of body temperature	(1) Monitor and dynamically adjust the operating room temperature, do a good job of keeping warm
		(2) Reduce limb exposure, for patients covered inflatable heating blanket
		(3) The infusion of liquid will be first heated to 37 °C
	Prevention of infection	(1) Ensure the operating room environment, control the number of patients involved in the operation
		(2) Strict disinfection towel, as far as possible to shorten the operation time and reduce the surgical trauma, the operation field repeatedly rinse
		(3) Preoperative 0.5–2 h intravenous antibiotics
		(4) If the operation time exceeds 3 h, or blood loss > 1500 ml with the second dose
		(5) The effective coverage time of antibacterial drugs includes the whole surgical process and 4 h after surgery, and the total prevention time is no more than 24 h
Postoperative	Management of anesthesia	(1) General anesthesia wake up: drink water before eating
		(2) Moxapride 5 mg Po Tid to improve gastrointestinal motility
		(3) Selection of anesthesia
	Management of rehydration	(1) Avoid a large amount of fluid replacement: infusion volume from 25 to 40 ml (kg/day) is appropriate
		(2) Control the infusion speed: the infusion speed of elderly patients is from 100 to 120 ml/h is appropriate
		(3) Monitor blood routine, liver function, kidney function, and cardiac function indicators
	Management of drainage tube	(1) No drainage or catheter was placed
	Control of nausea and vomiting	(1) Intraoperative intravenous use of dexamethasone 10 mg
		(2) Use ondansetron when necessary
	Management of sleep	(1) Sedative hypnotic or anti-anxiety drugs
	Management of pain	(1) Use of automatic analgesia pump for 3 days
		(2) Sequential use of anti-inflammatory and analgesic drugs, such as celecoxib 200 mg Po Bid (recommended reduction of 50% for liver damage and elderly patients)
	Management of activity	(1) Emphasis on early hip, knee, and ankle active flexion and extension function exercise, to increase muscle strength
		(2) Exercise passive joint flexion and extension of hip, knee, and ankle joints with the help of the physician and CPM, at least three times a day, at least 15 min each time
		(3) Asked frequently turn over, clap back
		(4) Acupuncture
		(5) Manipulation
		(6) Oral traditional Chinese medicine

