### Quality control

Prior to the clinical trial, we will carry out unified training to make sure all the physicians, nurses, and assessors involved fully understand the process of the trial, including selecting patient screening and selection, case report form writing, and manipulation details. To guarantee the quality of the whole trial, rigorous monitoring will be performed by three trained quality supervisors. During the trial, supervisors will check on case report forms and intervention twice a month. After verifying the case report forms, data will be input into the database by two full-time research members independently. The standard operating procedures (SOP) will be invariably followed. Dropouts, withdrawals (and the reasons), and any compliance of all patients occurring will be recorded in detail by the inspectors throughout the treatment and follow-up period.

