## Discussion

The surgical stress response associated with major surgery describes fundamental metabolic changes that lead to increased catabolism, immunosuppression, free radical production, and hypercoagulable states. These physiologic alterations have been linked to changes in organ function resulting in undesirable postoperative morbidity, complications, pain, fatigue, and extended convalescence. ERAS attempts to decrease the surgical stress response to minimize postoperative complications and improve surgical outcomes and functional rehabilitation after major surgery.

ITF commonly occurred in the elderly and caused high mortality rate due to the complications of loss of walking ability. Due to the great importance of good functional outcome and avoidance of serious postoperative complications, the general consensus is that early surgery is the first choice of treatment for the elderly patients and PFNA is a mature surgical procedure.

Several clinical literatures describing ERAS on arthroplasty have been published previously in the literature, but there is a lack of prospective high-quality data from larger cohorts on it for improved recovery after surgery. In particular, we are unaware of published ERAS program on the field of ITF. Based on the theory of TCM, manipulations, acupuncture, and oral Chinese medicine are of great significance in promoting fracture healing and improving patients’ whole body state. With the objective, we have conducted a systematic literature search including Wan Fang Data, CNKI databases, Vip Journal Integration Platform, Chinese BioMedical databases, PubMed, MEDLINE, EMBASE, Cochrane Library, and ISI web of knowledge, and ERAS pathway integrated Chinese and western medicine was established by Delphi expert-opinion process including ten experts. The new ERAS project is consist of a multidisciplinary evidence-based approach to preoperative management, intraoperative control, and rehabilitation.

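### Table 1's preoperative pain row gives celecoxib 200 mg twice daily without the 50% reduction that the postoperative row recommends for elderly patients, although every participant is over 75

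*Protocol article*

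**What the plan says.** All the relevant statements are in the protocol article.

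- **Table 1, Preoperative, Management of pain:** "Routine use of anti-inflammatory analgesics such as celecoxib 200 mg Po Bid". This is the only entry in the row, and it carries no adjustment for age or liver function.
- **Table 1, Postoperative, Management of pain:** the first entry is "Use of automatic analgesia pump for 3 days". The second is sequential use of anti-inflammatory and analgesic drugs, "such as celecoxib 200 mg Po Bid (recommended reduction of 50% for liver damage and elderly patients").
- **Inclusion criteria:** "The patients are over 75 years old".
- **Discussion:** the patients treated for this fracture are described as elderly: "early surgery is the first choice of treatment for the elderly patients and PFNA is a mature surgical procedure".

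**The concern.** The two pain rows name one drug at one dose and frequency, but only the later row carries the reduction. That reduction depends on who the patient is (elderly, or with liver damage), not on the phase of care. A patient who meets the condition the day after surgery met it the day before.

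In a trial with a wide age range this would touch a subgroup. Here the age criterion means that it touches everyone in the ERAS arm. The unreduced dose also stands in the row that describes routine use. Staff who follow that row as printed would give a patient over 75 twice what the same table recommends for elderly patients after surgery.

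At stake are the consistency of the dosing guidance, the drug exposure of an old population, and the ability of another centre to reproduce the pathway.

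**Working it through.** The plan states no power, alpha or sample-size figure that bears on this point. The check compares the two rows and works out the daily doses.

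**Inputs**
- Preoperative example: 200 mg twice daily, no qualifier (Table 1, Preoperative, Management of pain).
- Postoperative example: 200 mg twice daily, with a recommended 50% reduction for liver damage and elderly patients (Table 1, Postoperative, Management of pain).
- Age of participants: over 75, without exception (Inclusion criteria).

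**Does the age condition apply to these patients?** The article sets no numeric cut-off for the term. It does use the term for the patients treated for this fracture (Discussion). The postoperative rehydration row of Table 1 also sets its infusion speed for elderly patients and gives no other speed. The natural reading is that the label covers every participant, so the share of the ERAS arm that meets the condition is 100%.

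**Daily dose**
1. Preoperative row as printed: 200 mg × 2 = 400 mg/day.
2. Postoperative row with its reduction: 400 mg × (1 − 0.50) = 200 mg/day, that is, 100 mg twice daily.
3. Difference: 400 − 200 = 200 mg/day.
4. Ratio: 400 / 200 = 2.0.

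**Is the difference explained elsewhere?** No other part of the article extends the reduction to the preoperative phase, limits it to the postoperative phase, or gives a reason for treating the phases differently.

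**The case against.** The strongest reply is that the rows cover different situations. Before surgery the anti-inflammatory drug is the only listed analgesic for an unfixed fracture. After surgery an analgesia pump is listed as well, so a lower dose may suffice. This is clinically conceivable, but the text does not say it. The printed grounds for the reduction are age and liver damage, not the pump, and the row describes the drugs as used sequentially.

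A second reply is that neither row fixes a dose: celecoxib is an example and the reduction a recommendation. That stands and limits the weight of the point. A reader might infer that every ERAS patient will receive 400 mg/day before surgery. The article does not support this, because prescribers may choose another drug or apply the reduction unprompted.

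A third reply is that Table 1 is an outline and that dose adjustments may sit in the operating procedures. It is true that many rows have no doses. The point, however, rests on two doses that are printed and do not agree, not on a missing detail.

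Two further inferences are tempting and should not be drawn:
- **Supervisors cannot tell which dose is intended.** The Quality control section says that "supervisors will check on case report forms and intervention twice a month", but it also refers to standard operating procedures and to unified training. Those materials are not shown, so what they tell supervisors is unknown.
- **A total excess dose per patient can be stated.** The article gives neither the number of preoperative treatment days nor the share of patients who receive celecoxib, so no cumulative figure follows from it.

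Finally, the article does not say that 200 mg twice daily is harmful before surgery. The safety aspect rests only on the table's own caution for elderly patients.

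**Conclusion.** The point holds as a minor inconsistency. For a population that is entirely over 75, the preoperative example dose is 400 mg/day and the dose under the table's own recommendation is 200 mg/day, a factor of 2, with no reason given.

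This rests on two readings: that patients over 75 count as elderly in the sense of Table 1, and that a reduction tied to lasting patient traits applies before surgery as well as after it. The first is well supported by the article. The second follows from the wording of the qualifier but is not stated.

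The matter is confined to dosing guidance in the ERAS arm. It has no bearing on length of stay as an endpoint, on the sample size or on the analysis. The postoperative row is indirect, since its full dose would normally apply to no participant, but it is not wrong.

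**What to change.** Change one cell. In Table 1, Preoperative, Management of pain, add the postoperative row's qualifier: a recommended 50% reduction for liver damage and elderly patients. This makes 100 mg twice daily the example dose for this population. The postoperative row can stay as it is.

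If the full dose before surgery is deliberate, the same cell should say that the reduction applies only after surgery and give the reason.

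The cost is one table entry. The small clinical downside is less anti-inflammatory analgesia before surgery, which clinicians can supplement because celecoxib is only an example. Randomization, endpoints, sample size and analysis need no change.
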